## Abstract

**Background:**

Point-of-care testing (POCT) is increasingly being used in general practice to assist general practitioners (GPs) in their management of patients with diseases. However, low adherence to quality guidelines in terms of split test procedures has been observed among GPs in parts of the Capital Region in Denmark. Computer reminders embedded in GPs electronic medical records (ComRem) may facilitate improved quality control behaviour, but more research is needed to identify what types of reminders work and when. The overall aim of this study is to evaluate the efficacy of ComRem to improve GPs adherence to quality guidelines. This article describes the rationale and methods of the study that constitute this research project.

**Methods/design:**

The study is conducted as two randomised controlled trials (RCTs) among general practices in two districts of the Capital Region in Denmark. These districts contain a total of 739 GPs in 567 practices with a total of 1.1 million patients allocated to practice lists. In the first RCT (RCT A), ComRem is compared to postal reminder letters. In the second RCT (RCT B), ComRem is compared to usual activities (no reminders) with a crossover approach. In both of these studies, outcomes are measured by the number of split tests received by the laboratory.

**Conclusions:**

This study will contribute to knowledge on the efficacy of ComRem in primary care. Because the study does not explore GPs' perceptions and experiences with regard to ComRem, we will subsequently conduct a qualitative survey focusing on these aspects.

**Trial registrations:**

Study A: ClinicalTrials.gov identifier: NCT01152151

Study B: ClinicalTrials.gov identifier: NCT01152177

## Background

Point-of-care testing (POCT) is increasingly being used in general practice to assist general practitioners (GPs) in their daily work with patients. For adequate deployment of POCT, an external quality assessment (EQA) is recommended on a monthly basis [1]. In the Copenhagen area, EQA is enforced by a split test procedure as well as annual outreach consultant visits. In a split test, the actual POCT result is compared to a result from a blood sample from the same individual analyzed at the central laboratory. The quotient of these two results should ideally be 1.00, but a value inside the interval ranging from 0.85 to 1.15 is acceptable [1]. This quotient is returned to the practice for self-evaluation. However, the adherence to the monthly split test procedure has not been satisfactory among GPs in two districts of the Capital Region (Table 1). Therefore, the Copenhagen General Practitioners' Laboratory (hereafter simply referred to as 'the laboratory') planned to improve adherence.

**Table 1 T1:** GP and practice characteristics and distribution of the Point of Care tests at baseline (January to April 2010) stratified on the two RCTs

		Study A	Study B
		**Computer reminder/postal reminder**	**Computer reminder/usual care**
		**(Practices = 213)**	**(Practices = 286)**
		**(GPs = 318)**	**(GPs = 341)**
		**Mean (SD) or n (%)**	**Mean (SD) or n (%)**

GP and practice characteristics			
Gender	Male	177 (56)	171 (50)
	Female	141 (44)	170 (50)
Mean age (SD)		53.1 (7.8)	56.3 (8.2)
Mean years as GP		11.3 (8.8)	14.8 (9.6)
Total number of patients on practice lists		507,568	533,864
Mean number of patients per GP (SD)		1,596 (419)	1,566 (398)
Practice organization	Single Handed	139 (65)	239 (84)
	Group	74 (45)	47 (16)
Point of Care Tests at baseline			
Mean INR tests		86 (58)	---------------------
Mean Hemoglobin tests		63 (97)	40 (55)
Mean Glucose tests		78 (92)	47 (52)
Primary outcome		INR*	HGB/GLU**
Average number of split tests		0.35 (0.55)	1.07 (1.36)
Secondary outcomes			
Practice with three or four split tests		0 (0)	0 (0)
Practices with at least one split test		67 (31)	146 (51)

*four recommended in baseline period

**four are recommended for each of the two tests in baseline period

Dissemination of guidelines alone rarely brings about improvements in clinical practice [2], and even an multifaceted implementation of guidelines may not change clinical practice [3,4]. Multiple strategies for implementing guidelines appear to be more effective than single ones [5,6]. However, when evaluated rigorously, these strategies often produce only minor benefits and rarely on patient outcomes [7,8]. In general, well-designed empirical research looking into various implementation strategies is still needed in this area [9]. In order to improve adherence, the laboratory wants to employ computer reminders embedded in the GPs' electronic medical records (ComRem) additionally to the quality control enforcement activities. At the same time, the laboratory wanted to conduct a rigorous evaluation of this innovative approach.

Within the last decade, several systematic reviews have evaluated computer reminders [10-13]. However, these reviews have pooled several different types of computer reminders, *e.g*., computer-generated paper reminders, and e-mail alerts along with reminders generated at point of care. According to a recent Cochrane review, computer reminders have been shown to produce a small improvement on target behaviour [13]. The review concludes that more research is needed to identify what types of reminders work and when.

The overall aim of the randomised controlled trials (RCTs) described in this paper is to evaluate the efficacy of ComRem on adherence to clinical quality guidelines regarding POCT. This aim is translated into the following research questions:

1. What is the efficacy of ComRem compared to computer-generated postal reminder letters on general practices' adherence to clinical quality guidelines regarding POCT (RCT A)?

2. What is the efficacy and legacy of ComRem compared to usual activities (*i.e*., no special reminders) on GP adherence to clinical quality guidelines regarding POCT (RCT B)?

The reason why the study is divided into two RCTs is the laboratory's priority to implement a quality improvement intervention for all practices conducting international normalized ratio (INR) analyses. Hence, these practices could not be allocated to usual practice alone.

## Methods

The study is conducted as two RCTs among the practices in two districts in the Capital Region in Denmark. These districts contain a total of 739 GPs in 567 practices.

### Usual EQA practice

The guidelines recommend a split test procedure each month for each POCT instrument. The standard implementation of EQA consists of an annual facilitator visit in each practice. Also, information about the split tests was posted in three laboratory newsletters. Furthermore, an instruction on how the practices should execute split tests was posted as a link on the laboratory's web site.

### Computer reminders embedded in the GPs' electronic medical records (ComRem)

In the Danish health care sector, a common standard (MedCom) for electronic communication has been defined and used for a decade. MedCom is a co-operative venture between authorities, organizations, and private firms linked to the Danish healthcare sector, and uses a Danish adapted format of Electronic Data Interchange For Administration, Commerce and Transport (UN/EDIFACT) originally developed by the United Nations. MedCom offers secure electronic communication between hospitals, pharmacies, laboratories, and primary care, *e.g*., GPs and municipalities. Each practice has been allocated to a unique location number according to the MedCom standard. All electronic communication is delivered into a specific practice inbox and each communication has to be approved by the GP.

### Participants

Included in the study are all general practices that had performed at least four relevant POCT--INR, hemoglobin, or glucose--in the baseline study period (1 January to 31 April 2010) and had access to POCT within their own practice. These practices were identified in the GP database of the Capital area and in the laboratory database.

### Data collection

Data on performed split test procedures is retrieved from the laboratory database. These data do not contain any patient-related data because all split tests are conducted by an artificial identification code. Process indicators (sent reminder letters) are also obtained from the laboratory. The Capital Region databases provide information on the participating practices and corresponding GPs.

### Randomization

Within each study, practices are randomized into two similarly sized groups by means of computer generated random numbers using SAS version 9.2. To ensure that practice types are distributed equally over the intervention and control arms, randomization within each RCT is done separately for group practices and solo practices respectively. This randomization was conducted by the data manager of the Research Unit of General Practice without knowledge of the individual practice identification.

### Data from the capital region and Copenhagen general practice laboratory

The study period comprises a four-month baseline period before the start of the intervention and up to three four-month follow-up periods after the start of the intervention. During the study periods, the number of specific POCT tests done in each practice is monitored using the relevant bills sent to the Capital Region by the GPs. Concurrent, the occurrence of split tests on the specific POCT analyses and--for practices participating in an intervention arm--the number of ComRem or postal reminders sent in each of the follow-up periods are monitored in the laboratory database. Combined, this monitoring gives series of up to four measures (defined by several outcomes, see below) of adherence to the split test procedures--for the baseline period and for each of the follow-up periods--for each practice. Background information on practices and GP was retrieved by the Capital Region at the start of the study period. This information includes gender, age, year of graduation from university, working address, type of practice, and list size.

### Outcomes

Outcomes are measures of split test procedure adherence that are calculated from the monitor data.

### Primary outcome

Total number of split test procedures for the corresponding POCT analysis performed by the practice in a four-month period. In a given month, a split test procedure should only be performed if the practice conducted the POCT analysis. The maximum number of possible split test procedures for a single analysis in a four-month period is four.

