### Statistics

Cross-sectional differences in the outcomes between allocation groups in the baseline period and each of the follow-up periods are tested by means of t-tests (primary outcome) and chi-square tests (secondary outcomes). In order to investigate the development of split test procedure adherence over the up to four periods relative to the (changing) intervention, Poisson (primary outcome) and logistic (secondary outcomes) regression is used with GEE methods to account for the repeated measurements. To identify predictors for adhering to split test procedure guidelines, adjusted effects for the GP and practice characteristics are estimated in multivariate Poisson (primary outcome) and logistic (secondary outcomes) regression analysis on the outcomes at selected periods. Beyond the direct comparison of the randomization groups in the first follow-up period, comparisons in further follow-up periods are done to investigate various forms of potential legacy effect, *i.e*., the effect of an intervention in periods where the intervention is discontinued. All statistical analyses are performed using SAS, version 9.2 (SAS Institute Inc, Cary, NC).

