### RCT A: Comparing computer reminders with postal reminders

Included in RCT A are the practices conducting more than four POCT INR during the four-month baseline period (213 practices). Practices are randomly allocated to computer-generated postal reminder letters or to ComRem; both in addition to usual laboratory quality guideline activities. The comparison of outcomes after a first follow-up period: the intervention period estimates the relative efficacy of ComRem over postal reminder letters; a comparison after a second follow-up period in which both interventions are discontinued estimates the relative legacy effect of the interventions.

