### RCT B: Comparing computer reminders with usual activities and the potential legacy of electronic reminders

Included in the study are the 286 general practices conducting at least four POCT (either hemoglobin or glucose) during the four-month baseline period and that are not already included in RCT A. Practices are allocated to ComRem together with usual laboratory EQA practice or usual laboratory EQA practice only. The comparison of outcomes after a first follow-up period, the intervention period, estimates the relative efficacy of ComRem versus usual care only; a comparison after a second follow-up period in which the interventions are switched between groups estimates the relative efficacy of a (short-term) legacy effect of ComRem over the direct effect of ComRem; a comparison after a third follow-up period in which both interventions are discontinued estimates the relative efficacy of a long-term legacy effect of ComRem over the short-term legacy effect of ComRem.

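### RCT B counts split tests with no denominator for the number due, which can distort the predictor models and costs the arm comparison some precision

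*Protocol article*

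**What the plan says.** Under Primary outcome the protocol article defines the measure as a total: "Total number of split test procedures for the corresponding POCT analysis performed by the practice in a four-month period". The same section limits when a test is due, "In a given month, a split test procedure should only be performed if the practice conducted the POCT analysis", and gives a ceiling: "The maximum number of possible split test procedures for a single analysis in a four-month period is four".

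For RCT B, Table 1 combines hemoglobin and glucose in one primary outcome (mean 1.07, SD 1.36). Its footnote says that "four are recommended for each of the two tests in baseline period", which makes eight per practice, without the condition on months of use. The RCT B section admits practices "conducting at least four POCT (either hemoglobin or glucose) during the four-month baseline period", so a practice may run only one of the two analyses. For RCT A (INR only) the corresponding footnote reads "four recommended in baseline period".

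The Statistics section applies a t-test to the primary outcome in each period, a Poisson model with GEE over the periods, and a multivariable Poisson model on GP and practice characteristics. The purpose of the last is stated: "To identify predictors for adhering to split test procedure guidelines". No denominator is given for any of the three. The section on data from the Capital Region and the laboratory says that the number of POCT analyses per practice is monitored from bills, but the Statistics section gives that number no role in analysing the count.

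**The concern.** The article presents its outcomes as measures of adherence, and by its own rule adherence means tests done relative to tests due. In RCT B the number due differs between practices, while the outcome is the number done. A practice that does 1 of 1 due scores lower than one that does 2 of 8.

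Two analyses are affected differently. In the comparison of ComRem with usual activities, the number due is balanced between arms in expectation, so variation in it only adds noise. In the predictor models nothing balances it. A characteristic that goes with running both analyses, or with testing every month, raises the expected count at equal adherence and can be reported as a predictor of adherence.

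**Working it through.** **1. The plan's own figures.** The sample sizes are on the raw-count scale and reproduce with a two-sample t calculation at two-sided alpha 0.05 (assumed; the article gives no alpha) and 90% power. RCT A (SD 1, effect 0.5) needs 85.03, so 86 per arm, total 172. RCT B (SD 1.25, effect 0.5) needs 132.31, so 133 per arm, total 266. These figures are sound and do not bear on the point.

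**2. Possible number due at baseline.** Number due = number of analysis-months in which the POCT was used.
- RCT A: one analysis × 1 to 4 months = 1 to 4.
- RCT B: one or two analyses × 1 to 4 months = 1 to 8. The minimum arises if all qualifying tests of a single analysis fall in one month.

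That RCT B uses the combined count rests on the HGB/GLU entry in Table 1 and on the power calculation, which refers to hemoglobin and/or glucose.

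**3. Likely number due.** Inputs are the Table 1 volumes over four months: INR 86 (SD 58), hemoglobin 40 (SD 55), glucose 47 (SD 52). Assumptions: lognormal or gamma volumes, Poisson monthly counts, and the two RCT B analyses either independent or fully concordant.

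| RCT B assumption | 8 due | 4 to 8 due | 1 due | Mean due | CV |
|---|---|---|---|---|---|
| Lognormal, independent | 77.8% | 99.9% | 0.0% | 7.66 | 0.10 |
| Lognormal, concordant | 82.4% | 99.3% | 0.1% | 7.67 | 0.11 |
| Gamma, independent | 55.1% | 98.1% | 0.1% | 6.84 | 0.23 |
| Gamma, concordant | 73.8% | 96.5% | 0.3% | 7.34 | 0.19 |

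In RCT A, 98.7% to 99.8% of practices have all four due.

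These shapes give every practice some volume of both analyses, so they may understate the spread in RCT B. Table 1 does not exclude non-users. If 20% of practices ran no hemoglobin, users would have mean 40/0.8 = 50 and SD √[(55² + 40²)/0.8 − 50²] = √3281 ≈ 57, which is quite possible.

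**4. Predictor models.** At equal adherence, the spurious rate ratio is the ratio of mean numbers due. Take group against solo practice; group practices are 47/286 = 16.4% of RCT B.
- Every group practice has 8 due and the overall mean is 7.67 or 6.84, as in step 3. The solo mean is (7.67 − 0.164 × 8)/0.836 ≈ 7.6 or (6.84 − 0.164 × 8)/0.836 ≈ 6.6. The ratios are 8/7.6 ≈ 1.05 and 8/6.6 ≈ 1.21.
- Every group practice has 8 due, and 30% or 50% of solo practices have 4 while the rest have 8. The solo mean is 0.3 × 4 + 0.7 × 8 = 6.8 or 0.5 × 4 + 0.5 × 8 = 6. The ratios are 8/6.8 = 1.18 and 8/6 = 1.33.
- Bound: a characteristic that coincides exactly with running two analyses rather than one, all tested monthly, gives 8/4 = 2.

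**5. Arm comparison.** RCT B was simulated with 143 practices per arm, control mean 1.07, beta-binomial variation between practices (concentration 2, assumed) and 4,000 runs. The columns give power at a true ratio of 1.5.

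| Number due | t-test, raw count | t-test, done/due |
|---|---|---|
| All 8 | 64.0% | 64.0% |
| 30% have 4, 70% have 8 | 68.4% | 71.5% |
| Uniform on 1 to 8 | 77.2% | 84.6% |
| Half have 1, half have 8 | 62.2% | 74.8% |

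With no true effect both tests reject in 4.5% to 5.0% of runs, and the estimated ratio is 1.00 with or without a denominator. At a true ratio of 1.5 both estimates are 1.50 to 1.51.

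Only the differences between columns should be read. The assumed heterogeneity is wider than Table 1 shows. With 8 due, p = 1.07/8 = 0.134 and the variance is 8 × 0.134 × 0.866 × (8 + 2)/(1 + 2) ≈ 3.09, so the SD is about 1.76 against 1.36 in Table 1.

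**The case against.** The strongest reply is that this is a condensed article. A Poisson offset is the kind of detail left to an analysis plan, and the article does place the due-month rule inside its outcome definition. That stands for the Poisson models: one can say only that no denominator is stated, not that none will be used. It does not cover the definition of the outcome as a total, or the t-test on that total, which cannot take a denominator. Both are stated choices.

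A second reply is that the raw count is legitimate. It is what the laboratory receives, both sample sizes are built on it, and predictors are in neither research question. This stands for the arm comparison and is why the count should be kept there. It does not help an analysis whose stated aim is to explain adherence.

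A reader might also infer more than the article supports:
- *That the ComRem effect is biased.* Allocation is random within each RCT, and the simulated error rate and ratio are unaffected.
- *That practices with one test due are set against practices with eight throughout.* Eight is impossible in RCT A, the two trials are analysed separately, and at most 0.3% of RCT B practices have one due in step 3.
- *That POCT volume as such is read as adherence.* The number due is capped at four per analysis, so volume beyond monthly use adds nothing.
- *That predictors will show eightfold ratios.* That needs a characteristic matching one month of one analysis against four months of both, and none of those collected is shown to do so. Entering practice type and list size together may also absorb part of the effect.

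**Conclusion.** The point holds for RCT B and is moderate in size. The number due varies by the article's own rule, the outcome ignores it, and no denominator is stated in the analysis. The main consequence is in the predictor models, where a spurious rate ratio of roughly 1.05 to 1.3 is plausible for a characteristic such as group practice; 2 is only a bound. The randomised comparison stays valid and loses some precision, about 3 points of power if 30% of practices have four due. Losses of 7 to 13 points need a spread far wider than the Table 1 volumes imply. In RCT A the number due is practically constant and nothing needs to change.

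The sizes rest on assumed volume distributions, an assumed link between practice type and number due, and assumed heterogeneity in adherence. None of these is in the article. A larger share of one-analysis practices would raise them.

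**What to change.** For RCT B, derive for each practice and period the number of analysis-months in which hemoglobin or glucose testing was billed (0 to 8). Then:

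- **Predictor models:** model done out of due as binomial, or add log(analysis-months due) as an offset to the Poisson model. Exclude practice-periods with none due, where the log is undefined.
- **Randomised comparison:** keep the raw count, but adjust for baseline-period analysis-months, or for one versus two analyses at baseline. Both refer to the period before the intervention. The simulation compared done/due with the raw count, so the exact gain from this adjustment has not been calculated.
- **Reporting:** give split tests as a percentage of those due beside the raw count, by arm and period.

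The cost is one derived variable from data already collected, provided that the billing data can be separated by month. The follow-up denominator is measured after randomisation and could itself respond to the reminders, so in the arm comparison it should serve only as a sensitivity analysis.

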### Secondary outcomes

1. Whether the practice has a high quality of tests defined as 75% of the performed split test procedures within the reference interval (according to the laboratory quality guidelines).

2. Whether split test procedures are performed at all by the practice.

### Statistics

Cross-sectional differences in the outcomes between allocation groups in the baseline period and each of the follow-up periods are tested by means of t-tests (primary outcome) and chi-square tests (secondary outcomes). In order to investigate the development of split test procedure adherence over the up to four periods relative to the (changing) intervention, Poisson (primary outcome) and logistic (secondary outcomes) regression is used with GEE methods to account for the repeated measurements. To identify predictors for adhering to split test procedure guidelines, adjusted effects for the GP and practice characteristics are estimated in multivariate Poisson (primary outcome) and logistic (secondary outcomes) regression analysis on the outcomes at selected periods. Beyond the direct comparison of the randomization groups in the first follow-up period, comparisons in further follow-up periods are done to investigate various forms of potential legacy effect, *i.e*., the effect of an intervention in periods where the intervention is discontinued. All statistical analyses are performed using SAS, version 9.2 (SAS Institute Inc, Cary, NC).

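### Free improvement: the first-follow-up comparison in each RCT is an unadjusted t-test, although baseline split-test counts and the solo/group strata are already held; the cost is precision, not validity

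*Protocol article*

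**What the plan says.** The Statistics section of the protocol article sets out three layers of analysis.

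- **Between-group tests.** "Cross-sectional differences in the outcomes between allocation groups in the baseline period and each of the follow-up periods are tested by means of t-tests" for the primary outcome, and chi-square tests for the secondary outcomes. No covariate or stratum is named. The same section sets the later contrasts apart with "Beyond the direct comparison of the randomization groups in the first follow-up period", and the RCT A and RCT B sections say that the comparison after the first follow-up period estimates relative efficacy.
- **Repeated-measures models.** For the development of adherence over up to four periods, relative to the changing intervention, Poisson or logistic "regression is used with GEE methods to account for the repeated measurements".
- **Multivariate models.** "To identify predictors for adhering to split test procedure guidelines, adjusted effects for the GP and practice characteristics are estimated", at selected periods.

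Two design features bear on this. The monitoring data give a series of adherence measures "for the baseline period and for each of the follow-up periods--for each practice", so each practice's pre-intervention value of the outcome is on file. The Randomization section says that "randomization within each RCT is done separately for group practices and solo practices respectively".

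**The concern.** The test stated for the efficacy contrast leaves out the two pieces of design information most likely to help it. If practices that did split tests before the intervention tend to do them afterwards, the baseline count explains part of the follow-up variance. An unadjusted comparison leaves that part in the standard error, and leaves any chance baseline imbalance in the estimate.

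Within the t-test layer, the baseline serves only as something to be tested for difference. Under randomisation such a difference is chance, so that test neither corrects an imbalance nor guides the analysis.

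At stake are wider confidence intervals and lower power, mostly for effects smaller than the planned 0.5. There is also some doubt about whether the t-test or the GEE answers the efficacy question.

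**Working it through.** **Inputs from the protocol article**

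- RCT A: SD 1, effect 0.5, power 90%, 172 practices required; 213 included.
- RCT B: SD 1.25, effect 0.5, power 90%, 266 practices required; 286 included.
- Table 1, split tests at baseline, mean (SD): A 0.35 (0.55); B 1.07 (1.36). Practices with at least one: A 31%, B 51%. Solo practices: A 139 of 213; B 239 of 286.
- Allocation: "practices are randomized into two similarly sized groups", taken as 1:1.

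**Assumptions.** Two-sided 5% (the article gives no alpha or sidedness) and a baseline to follow-up correlation r of 0.2 to 0.7 (the article gives none).

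**Step 1: reproduce the stated sample sizes.** For an unadjusted two-sample t-test (noncentral t, 90% power), the smallest even total is 172 for RCT A (power 90.3%) and 266 for RCT B (90.1%). Both match exactly. The normal approximation gives 170 and 264; one-sided 5% gives 138 and 216, which does not match. The trials are therefore sized on the unadjusted t-test.

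**Step 2: effect of baseline adjustment.** Residual SD = SD × √(1 − r²), so variance falls by r²: 4% at r = 0.2, 9% at 0.3, 25% at 0.5 and 49% at 0.7. With N practices, SE = residual SD × √(4/N). Power is taken from the noncentral t with noncentrality 0.5/SE. For RCT B at SD 1.25 and r = 0, SE = 1.25 × √(4/286) = 0.148, noncentrality is 3.38 and power is 92%. The normal approximation differs by at most about 0.3 percentage points.

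Power for an effect of 0.5 at the included size:

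| r | A, SD 1, N 213 | B, SD 1.25, N 286 | B, SD 1.36, N 286 |
|---|---|---|---|
| unadjusted | 95.3% | 92.1% | 87.2% |
| 0.2 | 96.0% | 93.1% | 88.5% |
| 0.3 | 96.8% | 94.2% | 90.1% |
| 0.5 | 98.7% | 97.3% | 94.7% |
| 0.7 | 99.9% | 99.7% | 99.1% |

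95% CI half-width, 1.96 × SE, under the planning SDs:

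| r | A | B |
|---|---|---|
| unadjusted | 0.269 | 0.290 |
| 0.2 | 0.263 | 0.284 |
| 0.3 | 0.256 | 0.276 |
| 0.5 | 0.233 | 0.251 |
| 0.7 | 0.192 | 0.207 |

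The unadjusted sample size of equal precision is N/(1 − r²). At r = 0.5 this is 213/0.75 = 284 in A and 286/0.75 = 381 in B. At r = 0.2 it is only 222 and 298.

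**Step 3: smaller effects.** Simulation used 3,000 runs per setting, normal outcomes, stratified 1:1 allocation, planning SDs and an assumed solo/group difference of 0.25. At a true difference of 0.3, power rose in A from about 59% to 62% (r = 0.3) or 72% (r = 0.5), and in B from about 51% to 56% or 64%.

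**Step 4: contribution of the strata.** The share of variance explained is p(1 − p)D²/SD², with p the proportion of solo practices and D the assumed solo/group difference in split tests.

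- D = 0.25: A 0.653 × 0.347 × 0.0625/1 = 1.4%; B 0.836 × 0.164 × 0.0625/1.5625 = 0.5%.
- D = 0.5: A 5.7%; B 2.2%.

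**Step 5: validity.** In the same simulation with no true effect, the t-test rejected in 4.4% to 4.9% of runs, so ignoring the strata does not inflate the type I error.

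**The case against.** The strongest reply is that the baseline is not in fact ignored. The GEE runs over up to four periods, the baseline among them, and is tied to the changing intervention. A repeated-measures model of that kind is a recognised way to bring baseline information into the treatment contrast. Practice type is collected, and practice characteristics enter the multivariate models. A condensed article may leave covariate lists to a fuller plan, and the t-test matches the sample-size calculation.

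Much of this stands. A reader might infer that the baseline is used only for a significance test between arms; the GEE sentence contradicts that. A reader might also infer that the t-test is biased or invalid, or that the trials are underpowered without adjustment. Neither follows: the test is valid under randomisation, and unadjusted power under the planning SDs is already 95% (A) and 92% (B). The 87% for RCT B comes from replacing the planning SD with the Table 1 SD, which is a separate question from adjustment.

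The size of the gain is also uncertain. No correlation is reported. Reminders go only to practices that missed the previous month, which could weaken the correlation in reminded arms. In RCT A only 31% of practices had any baseline split test, so the baseline count may predict little there.

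What the reply does not remove is that the article states the test for the between-group comparison, and that test is unadjusted. The GEE is presented as a model of development over time, is not named as the efficacy comparison and states no stratum term. The multivariate models are there to find predictors. This is a stated choice, not merely a detail left to another document.

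**Conclusion.** The point holds as an efficiency improvement. The stated direct comparison forgoes precision that the trials could have at no cost. The residual variance saved is about r², or 4% to 49% for r between 0.2 and 0.7.

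For the planned effect the power gain is modest, because both trials include more practices than they required. The benefit lies mainly in narrower intervals and in smaller effects. RCT B has more to gain than RCT A. Nearly all of the gain would come from the baseline count; the stratum term mainly matches the analysis to the design.

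The figures rest on two-sided 5%, 1:1 allocation, a linear model and an assumed correlation. For RCT B they also depend on whether the SD is 1.25 or 1.36.

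**What to change.** In each RCT, name one primary efficacy analysis: the first-follow-up comparison of split-test counts, adjusted for the practice's baseline split-test count and practice type (solo or group). Either ANCOVA or Poisson regression with robust variance would serve. ANCOVA keeps the mean-difference scale on which the effect of 0.5 was planned. Adjust the binary secondary outcomes for the same two covariates by logistic regression.

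Keep the t-test as a sensitivity check, and keep the GEE for its stated purpose of describing development over periods. Drop the between-arm significance tests at baseline and show the baseline values descriptively.

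The cost is a few lines of analysis text and SAS code. No new data, practices or follow-up are needed.
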